**Fig. 6 Fig6:**
[figure not shown]
Multidisciplinary clinical pathway for the evaluation of sleep disorders in older people

### Outcomes

The primary outcome is the incidence of physical and functional worsening at 12 months (Fig. 7).

**Fig. 7 Fig7:**
[figure not shown]
SOMNUS-DARE analytic aspects

It will be measured in terms of SPPB score < 9 [51, 52] for healthy active elderly individuals and in terms of inability to complete a 400 m walk test in less than 15 min (without sitting, stopping for more than one minute, receiving help, or using a walker) [53] for physically frail sarcopenic elderly Individuals.

The secondary and exploratory outcomes have already been listed in Table 1.

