### Setting and participants

Physically frail sarcopenic [3 ≥ Short Physical Performance Battery (SPPB) score ≤ 8] and healthy active [SPPB score > 8] [51] subjects from 65 years of age and afferent the geriatric and sleep medicine outpatient clinics, not demented and independent in the Basic Activities of Daily Living (ADL), will be categorized on the basis of the reduced sleep quality, self-reported and screened by the Pittsburgh Sleep Quality Index [PSQI (Italian version)] [56, 57] and stratified for the usual level of physical activity assessed by Physical Activity Scale for the Elderly [PASE-I (Italian version)] [58, 59]. The following eligibility criteria are intended to select a population that is at risk of accelerated decline in aging trajectory due to sleep disorders and their related systemic consequences. This age-group shall be selected for the sufficient long-life expectancy: to participate in a longitudinal study that lasts up to 2 years. Targeting this subset of the elderly population we will be able to recruit a non-disabled but at-risk population for a research project employing digital and eHealth technologies for frailty and disability assessment and prevention. Furthermore, we are planning to evaluate the eligibility criteria for those subjects previously enrolled in the SPRINTT clinical trial by the Parma site, completed at the end of 2019 and who have not evolved to a condition of disability or dementia, as well as those older individuals screened in the Trajector-AGE study by the same site, started at the end of 2022 and who were found to be sarcopenic and physically frail.

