### Inclusion criteria

Age ≥ 65 years;MMSE score [60] adjusted by age and education ≥ 25/30;Absence of mobility-disability;Absence of need for assistance with Basic Activities of Daily Living (according to the ICFSR International Clinical Practice Guidelines) [52].

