### Comprehensive geriatric assessment

A multidimensional panel of tools administered through a holistic clinical evaluation and aimed to analyse the bio-psycho-social sphere aspects listed below.CognitionMini Mental State Examination (MMSE) [60] was originally proposed by Folstein and is widely used for the worldwide cognition assessment.Clock Drawing Test is a first-order, rapid-fire test for the assessment of executive and visuospatial functions [61].Trail Making Test (TMT, part A and B) is a test of visuo-motor speed (part A) and executive function (part B) [62]. In TMT-A, participants are asked to draw a line connecting circled numbers from 1 to 25 as fast and accurately as possible. The score corresponds to the time (0–300 s) required to connect the circles. In TMT-B, participants are asked to draw a line connecting ascending, alternating, numbers and letters (1-A-2-B-3-C, etc.). The score corresponds to the time (0–300 s) required to complete the task. The test is stopped if participants cannot complete it in 300 s or if five errors are made, in that case, the scores of 300 s and five errors are recorded.Geriatric Depression Scale – 15 items (GDS) is a widely used and validated tool which show a significant agreement with the clinical diagnosis of depression [63].Mobility and muscle performanceA 400-m walk test will be assessed using standardized conditions [64]. Participants will be asked to walk 400 m at their usual pace and without overexerting themselves. During testing, they may not use any assistive devices. Subjects will be instructed to begin the test at the start line from a standing position, to walk down the corridor. During the walk, if participants feel the need to stop and rest, they will be allowed to stand in one place and rest without sitting. They will be instructed to resume walking as soon as they will be able to do so. If they will be unable to continue after a 60-s rest stop or if they need to sit down, the test will be stopped. There will be no limits to the number of allowable rest stops, as long as the participant can complete the walk within 15 min without sitting. The test will be discontinued after 15 min, a time that corresponds to a very slow walking speed (0.45 m/s): translated into a walking capacity, it has little utility in daily life. Participants unable to complete the test within 15 min will be considered to be mobility disabled. Heart rate will be recorded at the beginning and at the end of the test. The number, timing, and reasons for the rest stops (fatigue, chest pain, feeling faint or dizzy, shortness of breath, or other) will be recorded. The inability to complete the 400-m walk has already been used as the defining criterion for mobility disability in major clinical studies, in particular the LIFE [65] and SPRINTT [18] trials.Short Physical Performance Battery (SPPB) [51] was developed to objectively measure lower-extremity physical performance [66]. The test takes about 5 min to be administered. The battery has an excellent safety record. The components of the battery are the following:i.Standing balance, in which participants are asked to maintain balance in three positions, characterized by a progressive narrowing of the base support, with feet together (side by side position), the heel of one foot beside the big toe of the other foot (semi tandem position), and the heel of one foot in front of and touching the toes of the other foot (tandem position). For each of the three positions, participants have 10 s at longest. Scores are summed for the measure of balance for a range of 0 to 30 s.ii.Usual gait speed is assessed by asking the participants to walk at their usual pace over a 4-m course. Participants are instructed to stand with both feet touching the starting line and to start walking after a specific verbal command. Participants are allowed to use a cane if necessary, but not the assistance of another person or any other devices. The faster of two walks is used to compute walking speed.iii.Chair stands, in which the repeated chair stands test is performed using a straight-backed chair, whose back is placed against a wall. Participants are first asked to stand once from a sitting position without using their arms. If they are able to perform the task, they are then asked to stand up and sit down five times, as quickly as possible. The time to complete the task is recorded. To each of the three performance measures is assigned a score ranging from 0 to 4, with 4 indicating the highest level of performance and 0 the inability to complete the test. For the test of balance, participants are assigned a score of 1 if they can hold a side-by-side standing position for 10 s but they are unable to hold a semi-tandem position for 10 s; a score of 2 is assigned if they can hold a semi-tandem position for 10 s, but they are unable to hold a full-tandem position for 3 s; a score of 3 is assigned if they can stand in a full-tandem position for 3 s but less than 10 s; a score of 4 is assigned if they can stand in a full-tandem position for 10 s. Four categories are computed for walking speed and chair stands, according to standardized and previously published cut-points [67]. A summary score ranging from 0 (worst performers) to 12 (best performers) is calculated by adding walking speed, chair stands and balance scores.Hand Grip Strength Test is a commonly used measure of upper-body skeletal muscle function and has been widely used as a general indicator of frailty with predictive validity for both mortality and functional limitation [68]. Grip strength is measured in the dominant hand using a hydraulic grip strength dynamometer: there are no known risks for the participant, except for a possible temporary discomfort during the test itself.PASE is composed of 10 items: it requires 5 min, can be self-administered and has an easy scoring process. Furthermore, the activities evaluation, except for exercise, including the ones typical of older adults, such as household and caregiving, help to ensure that the instrument provides a comprehensive assessment of overall physical activity [58, 59].Nutrition3-day dietary record through paper, pre-printed and blank will be delivered to participants. In these forms, participants will record the diet they followed during the 3 days before the clinical visit. In particular, for any food/beverage taken during the previous three days, participants will record time (date and hour), name of food/beverage, and quantity (portion, weight, volume).Mini Nutritional Assessment – Short Form (MNA-SF) is a well-established instrument that allows the rapid assessment of nutritional status in elderly patients in outpatient clinics, hospitals, and nursing-homes. It has been translated into several languages and validated in many clinics around the world. The test is composed of simple measurements and brief questions that can be completed in about 5 min [69].Global Leadership Initiative on Malnutrition (GLIM) criteria, a global consensus scheme for diagnosing malnutrition in adults in several clinical settings, will allow the diagnostic framing of malnourished individuals who have been identified as being at risk in the MNA-SF first screening step [70].MultimorbidityThe Cumulative Illness Rating Scale (CIRS) will be used to measure the chronic medical illnesses burden, considering their severity stage [71].PolypharmacyMedication Inventory will allow to identify both prescription and non-prescription pharmaceutical products used by enrolled individuals. It is an important indicator of overall health, and the nature of the drugs taken is a strong indicator of clinically manifest disease. At each clinical visit all participants will be asked to bring all the prescription and non-prescription medications taken in the previous two weeks. The name, strength and formulation of each product are transcribed. These medications are coded according to the formulation for use in subsequent data analyses. This approach (drug assessment) has proved valid in older adults [72].Functional statusThe Lawton Instrumental Activities of Daily Living (IADL) score (ranging from 0 to 8; the higher the score, the greater the participant’s self-sufficiency) assesses the ability to perform tasks such as using a telephone, doing laundry, and handling finances. Measuring eight domains, it can be administered in 5 min. The scale may provide an early warning of functional decline or signal the need for further assessment [73].Katz Activities of Daily Living (ADL) score (ranging from 0 if participant is totally dependent, to 6 if participant is independent) is used to collectively describe fundamental skills required to independently care for himself, such as eating, bathing, and mobility. It is used as an indicator of a person’s functional status and the inability to perform these activities results in the dependence from other individuals and/or mechanical devices, as well as may lead to unsafe conditions and poor quality of life. This score is a strong predictor of admission to nursing homes, need for alternative living arrangements, and hospitalization [74].Quality of lifeEuroQoL-5D-5L is a 5-item questionnaire exploring various domains of quality of life. In particular, subjects are asked to describe their current health status in terms of mobility capacity, self-care (e.g., washing, toileting, dressing), usual activities (e.g., work, study, hobbies), pain, anxiety or depression. Each of these domains is described by choosing one out of five possible degrees of impairment/severity. The EuroQoL-5D-5L score is calculated according to algorithms weighted on the European population, adjusting the value of the answers according to social and cultural influences of specific countries [75]. A negative EuroQoL-5D-5L score indicates a quality of life perceived as worse than death. The EuroQoL instrument also includes a 10-cm long visual analogue scale. Participants will thus be asked to draw a line from a box to the point on the thermometer-like scale (ranging from 0 – worst quality of life, to 100 – best quality of life) corresponding to their health-related quality of life.OptimismThe Life Orientation Test-Revised (LOT-R) comprises 10 Likert-scaled items, with 6 assessing the main construct of dispositional optimism and the remaining 4 serving as filler items [76].Sleep healthPSQI [56, 57] is a 19-item self-report questionnaire commonly used to measure sleep quality over the last month. Sleep quality, sleep latency, sleep duration, habitual sleep efficiency, sleep disturbances, use of sleeping medications, and daytime dysfunction are the assessed sleep health domains. They are scored as a global factor. If the global score is higher than 5, it is considered as an indicator of relevant sleep disturbances.Other parametersFrom baseline to the end of the study follow-up, at scheduled time points, participants will undergo assessment of vital signs (blood pressure, heart rate, and blood oxygen saturation) and main anthropometric measures (including body weight, calf circumference, waist circumference, hip circumference, and mid-arm circumference). Moreover, sociodemographic, economic and behavioural information for descriptive purposes (age, gender, race, living situation, household composition, marital status, educational level, smoking status, alcohol consumed, employment status, occupation, volunteer work, income level, and lifestyle habits) will be asked.

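### In the healthy stratum the chance of a primary event depends strongly on baseline SPPB, yet the primary test of sleep disorders is an unadjusted comparison of two proportions

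*Protocol article*

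**What the plan says.** The Outcomes section states: "The primary outcome is the incidence of physical and functional worsening at 12 months". For the healthy stratum, "It will be measured in terms of SPPB score < 9 [51, 52] for healthy active elderly individuals". For the frail sarcopenic stratum the event is defined "in terms of inability to complete a 400 m walk test in less than 15 min".

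Setting and participants defines the healthy group as "healthy active [SPPB score > 8] [51] subjects from 65 years of age". The SPPB is "A summary score ranging from 0 (worst performers) to 12 (best performers") in whole points, so healthy participants start at 9, 10, 11 or 12.

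The Comprehensive geriatric assessment section describes the 400 m walk without limiting it to one stratum and adds: "Participants unable to complete the test within 15 min will be considered to be mobility disabled". The Inclusion criteria require "Absence of mobility-disability" of everyone.

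Under Statistical methods, the primary proportions get Clopper-Pearson intervals and a two-proportion test. Multivariable logistic regression is added as an aid to interpretation. An ordinal logistic model on unit decreases in SPPB and a mixed model for repeated measures follow as further analyses. No adjustment is attached to the primary test.

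**The concern.** The entry cut and the event cut are the same line, so how far a participant must fall to count depends on where that participant started. A change from 9 to 8 is an event; a change from 12 to 9 is not. Baseline SPPB is therefore a strong predictor of the event.

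Sleep disorders are not randomised. The Background argues that poor sleep accompanies poorer muscle and physical function, so it is plausible that exposed participants enter nearer to 9. A crude comparison would then show more events among them even if the two groups decline identically. Splitting the cohort into healthy and frail does not remove this, because the imbalance lies inside the healthy group.

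A smaller point concerns the 400 m walk. A healthy participant who newly fails it while SPPB stays at 9 or above is mobility disabled by the protocol's own definition but is not a primary event. Table 1 does not list incident mobility disability among the secondary or exploratory outcomes.

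**Working it through.** **1. Loss needed for an event (from the documents).** The event is SPPB ≤ 8, so the loss needed is baseline − 8.

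| Baseline SPPB | Points lost to count | Largest loss that does not count |
|---|---|---|
| 9 | 1 | 0 |
| 10 | 2 | 1 |
| 11 | 3 | 2 |
| 12 | 4 | 3 |

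**2. Weight of the healthy stratum (from Sample size).** Inputs: N = 300, frail to healthy 1:1, exposed to unexposed 2:1, unexposed rates 9% (healthy) and 27% (frail), risk ratio 1.55. The plan's pooled 18% reproduces: (9 + 27)/2 = 18. Each stratum has 100 exposed and 50 unexposed.
- Healthy: 50 × 0.09 + 100 × 0.09 × 1.55 = 4.5 + 13.95 = 18.45 events.
- Frail: 50 × 0.27 + 100 × 0.27 × 1.55 = 13.5 + 41.85 = 55.35 events.
- Healthy share: 18.45/73.8 = 25%.

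**3. Chance of crossing with no true change (assumed SDs).** The documents give no test-retest figure. Assume follow-up minus baseline is normal with mean 0 and SD 0.6 to 1.0 points. Then P(event | baseline b) = Φ((8.5 − b)/SD).

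| Baseline | SD 0.6 | SD 0.8 | SD 1.0 |
|---|---|---|---|
| 9 | 20.2% | 26.6% | 30.9% |
| 10 | 0.6% | 3.0% | 6.7% |
| 11 | <0.1% | 0.1% | 0.6% |
| 12 | <0.1% | <0.1% | <0.1% |

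**4. Baseline imbalance (assumed mixes).** Baselines 9/10/11/12 are 25/25/25/25% in exposed and 15/20/30/35% in unexposed. At SD 0.8:
- Exposed: 0.25 × (26.6 + 3.0 + 0.1 + 0.0) = 7.4%.
- Unexposed: 0.15 × 26.6 + 0.20 × 3.0 + 0.30 × 0.1 + 0.35 × 0.0 = 4.6%.
- Healthy-stratum ratio with no effect at all: 7.4/4.6 = 1.6.
- If only the share at 9 differs (25% against 15%, the rest spread equally), the unexposed rate is 4.9% and the ratio is about 1.5.

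**5. Restoring the planned rate.** The plan expects 9% in unexposed healthy participants, not 4.6%. Adding 4.4 points of true events to each group gives (7.4 + 4.4)/9 = 11.8/9 = 1.31.

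**6. Effect on the pooled primary ratio.** With half of each exposure group frail and 27% events in both frail groups:
- Without restoring: (7.4 + 27)/(4.6 + 27) = 34.4/31.6 = 1.09.
- With 9% restored: (11.8 + 27)/(9 + 27) = 38.8/36 = 1.08.

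**7. Range over the assumed SD (same mixes).**

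| SD | Healthy ratio | Healthy, 9% restored | Pooled | Pooled, 9% restored |
|---|---|---|---|---|
| 0.6 | 1.65 | 1.23 | 1.07 | 1.06 |
| 0.8 | 1.61 | 1.31 | 1.09 | 1.08 |
| 1.0 | 1.55 | 1.38 | 1.10 | 1.09 |

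In this illustration the crossing probability at each baseline score is the same in both groups. A comparison conditional on baseline SPPB would give a ratio of 1.

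**The case against.** The strongest reply is that this is how an incidence outcome works. A participant must be free of the state at entry, so entry and event cuts coincide by construction, and those nearer the line always cross more often. That stands. The shared cut is not an error, and the cut-off is referenced.

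A second reply is that the protocol does analyse the amount of decline. The ordinal model on unit SPPB decreases would register a change from 12 to 9, the mixed model uses all visits, and the Discussion promises covariate adjustment. That also stands, but none of these is the primary test. A covariate list can wait for the analysis plan; here the protocol itself names a crude test for the primary comparison.

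A third reply is that the SDs and baseline mixes come from no passage. True: they show a mechanism and a possible size, not an estimate.

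Three stronger readings are tempting and are not supported:
- That healthy-stratum events are mainly measurement noise. Under the assumptions above, noise crossings run from about 3% to 10% against a planned 9%, too wide a range to conclude this. The 9% is also a rate of observed SPPB below 9 and may already include measurement error.
- That 1.6 is the bias in the primary result, or that noise reduces 1.55 to 1.28. Both concern the healthy stratum alone. The 1.28 assumes that half of the 9% is noise: 1 + 0.55 × 0.5 = 1.275. Pooled, it becomes (9 × 1.275 + 27 × 1.55)/36 = 1.48.
- That mobility disability counts as a good outcome in half the cohort. A walk failure is missed only when SPPB stays at 9 or above, and the documents do not say how often that happens.

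**Conclusion.** The point holds as a weakness of the primary comparison, not as a fault in the event definition. That the required loss runs from 1 to 4 points, and that the primary test ignores baseline SPPB, follows from the text without assumptions. The size of any bias does not. It needs exposed participants to enter nearer the cut, which is plausible but not stated. For the assumed imbalance, the spurious healthy-stratum ratio is about 1.6, or about 1.3 at the planned 9% rate. The pooled primary ratio is about 1.08 to 1.09 (1.06 to 1.10 over SDs of 0.6 to 1.0). These pooled figures also assume the same frail/healthy split in both exposure groups. Against a planned ratio of 1.55 this is modest, but it is avoidable with data already collected. Fig. 7, on analytic aspects, is not available here and could not be checked.

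**What to change.** In Statistical methods, make the primary sleep-disorder comparison conditional on the frail/healthy stratum and on baseline SPPB score, with at least the levels 9, 10, 11 and 12 kept apart in the healthy stratum. A stratified (Mantel-Haenszel type) or regression-adjusted risk ratio with its 95% interval would serve. With about 18 expected events in the healthy stratum, the method should tolerate sparse cells. Keep the crude two-proportion test as supportive.

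Leave the primary event as it is. Adding 400 m failure to the healthy-stratum event would make it a composite and lose the referenced 9% planning rate, with nothing in the documents to replace it. Instead, report incident 400 m failure in the healthy stratum as a supportive outcome.

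The cost is analysis wording and one added table, since baseline SPPB and the 400 m walk are already in the assessment. The change is best made before outcome data are examined. Two limits remain. A single SPPB carries measurement error, so conditioning on it reduces baseline confounding but need not remove all of it, and it does not undo dilution from chance crossings.

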### Safety

All devices that will be used in the study are certified as medical devices.

All clinical tests that will be performed in the study are routinely used in the outpatient evaluation of older subjects.

All evaluations will be performed in the presence of a physician.

Only three minimally invasive measures, venous blood sampling, percutaneous infusion of PET radiopharmaceuticals and percutaneous infusion of MRI contrast, are included in the experimental protocol.

Any procedure that according to current legislation will require the acquisition of the subject's informed consent, will be performed only after the subject has been thoroughly informed about the risks and upon signed informed consent.

### Ethics and dissemination

This study will be conducted in accordance with the principles of Good Clinical Practice (GCP, Guideline for good clinical practice E6(R2), EMA/CHMP/ICH/135/1995). The Principal investigator agrees to adhere to the procedures and instructions contained therein and to carry out the study according to GCP Guidelines, the Declaration of Helsinki and the National Regulations governing clinical studies. Any changes to the protocol will be made in the form of an amendment. Any unexpected changes in the conduct of the study will be recorded in the "Clinical Study Report". The study protocol, any protocol amendment, informed consent and any other information for participants must be approved by the Ethical Committee. As far as the amendments are concerned, the Principal Investigator will be able to immediately apply them upon written communication to the Ethical Committee and without waiting for its approval, if the participating subjects’ safety will be at stake. Furthermore, if the Principal Investigator will believe that, for participants’ safety reasons, it will be necessary to immediately amend the protocol, he must notify the Ethical Committee within 10 working days. Each subject must provide written informed consent in order to participate in the study. The Principal Investigator will be responsible for archiving and storing the essential documents of the study, before, during the conduct and after the completion or interruption of the study itself, in accordance with the current legislation and the GCP Guidelines. All data collected will be strictly anonymous. All the subjects will be identified with a number. The Principal Investigator must retain the participants' original data and a copy of the signed written informed consent. Some data will be written directly on the CRF, which therefore will act as the original data. Inspections/verifications audits may take place to ensure that the study will be conducted in accordance with the protocol and applicable regulatory provisions (during its execution or after the study will be completed). If a Regulatory Authority will require an inspection, the Principal Investigator must immediately inform the Promoter and his Ethical Committee. The results of the study will be disclosed at the conclusion of the trial by means of publications in international scientific journals and abstract for national and international congresses. The study documents must be kept in a safe place to ensure confidentiality is maintained and may not be disclosed to others without written authorization, except to the extent necessary to obtain the subjects' consent to participate in the study. The Promoter will reserve the right to interrupt the study in respect of the participants' well-being. The telephone number and email of the contact persons for conducting the study will be reported in the Investigator Folder provided to the center.
